# Adjuvant SOX chemotherapy versus concurrent chemoradiotherapy after D2 radical resection of locally advanced esophagogastric junction (EGJ) adenocarcinoma: study protocol for a randomized phase III trial (ARTEG)

**DOI:** 10.1186/s13063-021-05617-7

**Published:** 2021-10-30

**Keywords:** Esophagogastric junction adenocarcinoma, D2 radical resection, Adjuvant chemoradiotherapy

## Abstract

**Background:**

Survival benefit of adjuvant radiotherapy for locally advanced gastric cancer following gastrectomy plus D2 lymphadenectomy has always been controversial. Esophagogastric junction (EGJ) adenocarcinoma, which is usually classified as gastric cancer in East Asia, often has a higher locoregional recurrence rate after operation because of its special anatomical characteristics. The aim of this study is to determine whether adjuvant radiotherapy can improve survival of locally advanced EGJ adenocarcinoma after D2 radical resection.

**Methods:**

In this phase III, randomized, open label, controlled trial, we plan to recruit 378 patients with Siewert type II and III adenocarcinoma of EGJ, who had undergone transabdominal radical surgery and D2 lymphadenectomy, and were divided into pathological stage IIB to IIIC. All patients will be randomized 1:1 to receive either adjuvant chemotherapy alone (control group) or adjuvant chemotherapy plus chemoradiotherapy (experimental group). Patients allocated to control group will receive eight cycles of S-1 plus oxaliplatin (SOX), while the experimental group will receive two cycles of SOX followed by 45-Gy RT combined with S-1 and four additional cycles of SOX. The primary endpoint is 3-year disease-free survival rate (DFS). The secondary endpoints are 3-year overall survival rate (OS), 3-year locoregional recurrence-free survival rate (LRFS), 3-year distant metastasis-free survival rate (DMFS), and quality of life (QoL).

**Discussion:**

In the past, the adjuvant treatment of EGJ adenocarcinoma needs to draw on the experience of esophageal adenocarcinoma or gastric adenocarcinoma. In this study, EGJ adenocarcinoma is considered as an independent disease, and the conclusion will provide evidence for optimal adjuvant therapy of locally advanced EGJ adenocarcinoma after D2 radical resection.

**Trial registration:**

ClinicalTrials.govNCT03973008. Registered on 1 June 2019 (retrospectively registered), URL: https://clinicaltrials.gov/ct2/show/NCT03973008?term=NCT03973008&draw=2&rank=1

**Supplementary Information:**

The online version contains supplementary material available at 10.1186/s13063-021-05617-7.

## Background

Gastric cancer is one of the most threatening cancers, which ranked fifth in global cancer incidence and third in global mortality [1]. Surgical resection still remains the only radical treatment option for gastric cancer, while radical resection plus D2 lymph node dissection is currently the standard surgical procedure [2].

For locally advanced gastric cancer, the locoregional recurrence rate and distant metastasis rate are still high after D2 radical resection [3, 4], leading to poor prognosis of these patients. Therefore, adjuvant chemotherapy after radical surgery is currently recommended for all locally advanced gastric cancer. Pivotal CLASSIC trial, which was conducted in the East Asia, has demonstrated the superiority of adjuvant CAPOX chemotherapy in improving OS for postoperative patients with stage II/III gastric cancer [5]. Recently, ARTIST 2 trial has confirmed that adjuvant SOX can prolong DFS than S-1 monotherapy in D2-resected, node-positive gastric cancer patients [6].

However, the value of adjuvant radiotherapy after radical gastrectomy for gastric cancer has always been controversial [7]. Although the landmark INT-0116 trial confirmed the survival benefit of postoperative radiotherapy in resectable gastric cancer, most patients in this study underwent D0 or D1 resection [8]. Subsequent clinical studies have shown that adding adjuvant radiotherapy to chemotherapy does not seem to bring additional survival benefits to gastric cancer patients undergoing D2 radical resection [9].

In the past, the treatment of esophagogastric junction (EGJ) adenocarcinoma was based on the principles of esophageal cancer or gastric cancer. But it is by now increasingly recognized that EGJ adenocarcinoma is an independent tumor entity [10]. Due to the particularity of its anatomical location, the thoroughness of surgery for EGJ adenocarcinoma, especially in the aspect of surgical margin and extent of lymph node dissection [11], is not comparable to distal gastric cancer. Logically, there is a possibility of benefit from adjuvant radiotherapy for EGJ adenocarcinoma. Therefore, we initiated this prospective, randomized controlled trial to determine whether adjuvant chemotherapy plus chemoradiotherapy is superior to adjuvant chemotherapy after D2 radical resection for locally advanced EGJ adenocarcinoma, and to compare adjuvant chemotherapy plus chemoradiotherapy with adjuvant chemotherapy in terms of local recurrence, distant metastasis, and adverse reactions.

### Rationale for this trial

EGJ adenocarcinoma is a kind of tumor with high heterogeneity [12]. At present, Siewert classification is commonly used for selecting therapeutic strategies [13]. The staging and treatment strategies of type I often refer to esophageal cancer, while type II/III tumors are treated using strategies of gastric cancer, especially in East Asia. For Siewert type II/III cancer with a length of esophageal invasion ≤ 3 cm, there is a general consensus in Japan that it should be treated by an abdominal, transhiatal approach [11]. Transabdominal surgery has the advantages of thoroughness of abdominal lymph node dissection and a low rate of complications, but it also has some shortcomings such as limited proximal margin, poor surgical view of lower mediastinum, and inability to perform middle or upper thoracic lymphadenectomy.

In Europe, neoadjuvant chemoradiotherapy is the standard treatment modality for esophageal and EGJ cancers [14]. The CROSS study, which compared preoperative chemoradiotherapy plus surgery with surgery alone for esophageal and EGJ cancers, showed that the R0 resection rate was significantly increased, and the overall survival rate was also improved (49.4 months vs. 24 months) in the neoadjuvant chemoradiotherapy group [15]. However, postoperative modality is advocated by clinicians in Asian. We therefore initiated a prospective, randomized controlled study to assess the hypothesized improvement of disease-free survival for locally advanced EGJ adenocarcinoma by adding radiotherapy to adjuvant chemotherapy.

## Methods

### Study objectives

The objectives of this study are:
To assess whether adjuvant chemotherapy plus chemoradiotherapy is superior to adjuvant chemotherapy after D2 radical resection for locally advanced EGJ adenocarcinoma in terms of 3-year DFS.To compare adjuvant chemotherapy plus chemoradiotherapy with adjuvant chemotherapy in terms of 3-year OS, 3-year LRFS, 3-year DMFS, adverse reactions, and quality of life (QoL).

### Study design

This is a prospective, randomized controlled trial to evaluate the efficacy of adjuvant radiotherapy for locally advanced EGJ adenocarcinoma after D2 resection. The trial was conducted at the Cancer Hospital of the University of Chinese Academy of Sciences (Zhejiang Cancer Hospital). We anticipated that adjuvant radiotherapy can improve the 3-year DFS by 10%, thus providing strong evidence for adjuvant therapy for locally advanced EGJ adenocarcinoma. Our study has been registered at http://clinicaltrials.gov (ID: NCT03973008).

After providing the signed informed consent, eligible subjects will be randomly assigned to receive adjuvant chemotherapy plus chemoradiotherapy (experimental group) or adjuvant chemotherapy alone (control group) in a ratio of 1:1. Randomization will be stratified by whether the EGJ is invaded or not and by postoperative stage. Patients in adjuvant chemotherapy group (control group) will receive eight cycles of SOX regimen chemotherapy; while patients in adjuvant chemotherapy plus chemoradiotherapy group (experimental group) received two cycles of SOX, then concurrent chemoradiotherapy (45 Gy of radiation with S-1 concurrent oral chemotherapy), followed by four additional cycles of SOX. All adjuvant therapy should begin within 4–6 weeks after surgery. Patients enrolled in this study should complete 3-year follow-up after randomization. The date and location of the first recurrence, as well as the date of death, will be documented. The study flow chart is shown in Fig. 1, and the schedule of enrollment, interventions, and assessments is shown in Fig. 2. The Standard Protocol Items: Recommendations for Interventional Trials (SPIRIT) checklist is provided in Additional file 1.

**Fig. 1 Fig1:**
[figure not shown]
Flow chart of the study

**Fig. 2 Fig2:**
[figure not shown]
Schedule of enrollment, interventions, and assessments

### Study population

#### Inclusion criteria

Voluntary participation and written informed consent.Aged older than 18 years and younger than 70 years, gender unlimited.Confirmed that the tumor center was located between 1 cm above and 5 cm below the EGJ, regardless of invasion to the EGJ, and histopathological diagnosis of adenocarcinoma.Received transabdominal D2 radical operation, and R0 resection was performedAscites cytology was negative.Postoperatively classified as pathological stages IIB~IIIC.Eastern Cooperative Oncology Group (ECOG) performance status score 0–1.Laboratory tests: hemoglobin (Hb) > 9 g/dL; white blood cell (WBC) > 3 × 10^9^/L; absolute neutrophil count (ANC) > 1.5 × 10^9^/L; platelet (Pt) > 100 × 10^9^/L; bilirubin < 1.5 times the upper limit of normal value; alanine-glutamic transaminase (ALT) and alanine transaminase (AST) < 2.5 times the upper limit of normal value; and serum creatinine < 1.5 times the upper limit of normal value.Daily energy intake > 1500 kcal.

#### Exclusion criteria

Received neoadjuvant therapy.Intraperitoneal implantation and distant metastasis were found.History of malignant tumors (except skin basal cell carcinoma, thyroid papillary adenocarcinoma, and cervical carcinoma in situ, which survived for more than 3 years).History of serious heart and lung diseases, abnormal hematological examination, and immunodeficiency.Uncontrollable infections, seizures, or loss of self-awareness due to mental illness.Adverse drug addiction, long-term alcoholism, and AIDS patients.History of severe allergies.Pregnant or breastfeeding women.Participated in other clinical trials within 30 days.Any other condition that researchers consider inappropriate to participate in this trial.

#### Exit criteria

Cannot be treated according to the scheme of the study.Grade 4 allergic reactions or severe adverse reactions to research drug.Disease progression in the course of the study.Pregnant and/or not using adequate contraceptive measures.Researchers judged that subjects should not continue the study.Subjects request withdrawal.

### Chemotherapy regime

SOX regimen was used for adjuvant chemotherapy:
Oxaliplatin 130mg/m^2^ given intravenously on day 1S-1 given orally twice a day (half an hour after breakfast and dinner) for 14 consecutive days, and the dose of S-1 is shown in Table 1Repeated every 3 weeks

**Table 1 Tab1:** The dose of S-1

Patient’s body surface area (m^**2**^)	S-1 single oral dose
<1.25	40mg
≥1.25 to <1.5	50mg
≥1.5	60mg

### Concurrent chemoradiotherapy regime

Technique of irradiation: intensity-modulated radiation therapyPreparation prior to CT simulation: fast 4 h and drink 100 ml of water (including 5 ml of contrast agent) 30 min prior to scan; patients with remnant stomach drink additional semiliquid diet (like congee) 10 min before scanningTechnique of simulation: patients in the supine position with forearm on forehead, and use custom immobilization device (e.g., thermoplastic mask) to fix body from lower thorax to lower abdomen. The scanning range is from the apex of lung to the pelvic inlet, with 5-mm slice thickness. Intravenous contrast should be used whenever available unless allergic to contrast, old age, or with serious complications.Irradiation field: the clinical target volume (CTV) include anastomosis with a 3-cm margin in the cranio-caudal direction, and regional lymph node drainage area [No.110 (below carina), 20, 1-3, 7-9, 11 (proximal 1/3), 16a1-2]. The planning target volume (PTV) will be obtained by expanding the CTV by 5–7mm in radial direction, and by 10mm in cranio-caudal direction.Dose prescription and fractionation: a total dose of 45 Gy at 1.8 Gy per day, 5 days per week, for 5 weeks. Dose prescription and recording should comply with the recommendations of the ICRU 83.Organ at risk (OAR) volume definition and dose constraints: the complete volumes of the remnant stomach, the liver, the kidneys, the lungs, and the heart have to be delineated. Intestine and spinal cord must be outlined the volume between above and below 2cm range of PTV. In this study, the normal tissue dose constraints are shown in Table 2.Concurrent chemotherapy: S-1 given orally twice a day (half an hour after breakfast and dinner), Monday to Friday, during radiotherapy, and the dose of S-1 is shown in Table 1.

**Table 2 Tab2:** Normal tissue dose constraints

Organs	Dose constraints
Remnant stomach	V40 < 50% (no hot spot)
Liver	V30 < 40%
	Dmean < 18Gy
Kidney	V20 < 30%
Lung	V20 < 20%
Heart	V30 < 30%
Intestine	Dmax ≤ 50Gy
Spinal cord	Dmax < 40 Gy

### Outcome measures

#### Primary endpoint

The 3-year DFS is the primary endpoint of this study. It is defined as the percentage of patients without locoregional recurrence, distant metastasis, or tumor-related death at 3 years measured from the date of randomization. Once a patient is lost after the last follow-up, his/her survival time will be censored at the last date the patient is known to be alive.

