#### Secondary endpoints

The secondary endpoints of this study included 3-year OS, 3-year LRFS, 3-year DMFS, and QoL.

Three-year OS is defined as the percentage of patients in this study who are still alive at 3 years measured from the date of randomization. In this study, locoregional recurrence was defined as recurrence at the anastomotic site, tumor bed, remnant stomach, or regional lymph nodes site, and distant metastasis is defined as non-regional lymph node recurrence, peritoneal seeding, and metastasis to other organs. Three-year LRFS and DMFS are defined as the percentage of patients who are without locoregional recurrence or distant metastasis at 3 years measured from the date of randomization respectively. EORTC QLQ-C30 and QLQ-STO22 questionnaires will be used to evaluate QoL of patients at baseline, every 4 weeks during treatment and every visit after treatment.

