### Follow-up

Patients should be followed up once every 3 months within 2 years after operation and once every 6 months 2 years after operation until 5 years. Follow-up contents include physical examination, performance status monitoring, weight monitoring, routine blood test, blood chemistry, tumor markers (including CEA and CA19-9), adverse events, and QoL assessment. Chest, abdominal, and pelvic CT should be performed every 6 months, and gastroscopy is recommended once a year. If new symptoms or symptoms worsen, patients should receive follow-up visit at any time. The recurrence and/or metastasis must have biopsy or clinical imaging evidence, and the time and location of recurrence and/or metastasis should be recorded in detail.

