### Statistical analysis

In this study, the sample size was estimated by statisticians. The 3-year DFS of the experimental group is expected to be increased from 47 to 60% (δ=0.13), which provides strong evidence for adjuvant treatment of locally advanced EGJ adenocarcinoma. With a one-sided alpha =0.05 and 1 − *β*=0.8, 172 per group would be necessary, and 206 endpoint events need to be observed. Given an estimated dropout rate of 10%, the required total sample size would be 378. Patients enrolled in this study would be randomly divided into experimental group and control group, stratified by whether the EGJ is invaded or not and by postoperative stage. The ratio of the two groups was 1:1.

The analysis was based on the intention-to-treat (ITT) population. The ITT population should include all patients receiving randomization. Per-protocol (PP) population should include all patients who received at least two cycles of chemotherapy and completed radiotherapy for experimental group and received at least four cycles of chemotherapy for control group.

Comparison of baseline data between the two groups: if the quantitative data is normal distribution, *t* test is used; if it is not, rank sum test is used; *χ*^2^ test is used for qualitative data. Survival analysis is carried out by SPSS software package. Log rank *χ*^2^ analysis is used for comparison between the two groups, and Cox regression model is used in multivariate analysis. *χ*^2^ test is used to compare the recurrence rate, metastasis rate, and the incidence of side effects between the two groups. Two-tailed test is used, and *p* < 0.05 is considered statistically significant.

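### Primary DFS counts only tumour-related deaths, so other deaths leave the primary comparison, which is biased if they differ between arms

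*Protocol article*

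**What the plan says.** The section Primary endpoint defines 3-year DFS as the "percentage of patients without locoregional recurrence, distant metastasis, or tumor-related death at 3 years measured from the date of randomization". For a patient who is lost, it adds that "his/her survival time will be censored at the last date the patient is known to be alive".

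All-cause death enters only under Secondary endpoints, where 3-year overall survival is the "percentage of patients in this study who are still alive at 3 years measured from the date of randomization". No section makes a death without recurrence, judged unrelated to the tumour, a DFS event, and none says how such a death is handled.

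Related statements:
- Study design: "The date and location of the first recurrence, as well as the date of death, will be documented".
- Follow-up: "Chest, abdominal, and pelvic CT should be performed every 6 months", and "The recurrence and/or metastasis must have biopsy or clinical imaging evidence".
- Exit criteria include "Grade 4 allergic reactions or severe adverse reactions to research drug".
- Statistical analysis: "The 3-year DFS of the experimental group is expected to be increased from 47 to 60" percent. The analysis is by intention to treat, with a log-rank comparison.

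**The concern.** By restricting which deaths count, the definition takes some deaths out of the primary test. In the log-rank analysis a patient who dies of treatment toxicity or another non-tumour cause before recurring would be censored. Read literally as a percentage, the endpoint would place that patient among those without an event. On either reading the death does not count against the assigned arm, although the analysis is meant to be by intention to treat.

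The arms differ in a treatment that can itself cause harm, so non-tumour deaths may not balance. If they do not, the arm with more of them looks better on DFS than it is. The trial is also open label, and whether a death was tumour-related is a judgement that may be made with the arm known. Death from any cause needs no such judgement.

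A second, smaller matter is the censoring date. Knowing that a patient is alive does not show that the patient is free of recurrence, because recurrence has to be established by biopsy or imaging. Time between the last scan and the last contact is counted as disease-free without having been checked.

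**Working it through.** **Planning figures.** From Statistical analysis: 3-year DFS 47% (control) and 60% (experimental), 206 events, 172 per group, 378 in total.
- Hazard ratio = ln(0.60)/ln(0.47) = 0.677.
- Schoenfeld events at two-sided 0.05 and 80% power = 4 × (1.960 + 0.842)² / (ln 0.677)² = 206, which matches the plan. The one-sided 0.05 stated beside it gives 162. That conflict is a separate matter and does not affect this point.
- The difference at stake is 60 − 47 = 13 points.

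**Non-tumour deaths.** The article gives no rate, so the values below are assumptions. Let q be the 3-year probability of a non-tumour death before recurrence, taken as independent of recurrence, with such deaths censored under the stated definition. Then all-cause DFS = tumour-only DFS × (1 − q).

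| q experimental / control | Experimental | Control | All-cause difference |
|---|---|---|---|
| 3% / 1% | 0.60 × 0.97 = 0.582 | 0.47 × 0.99 = 0.465 | 11.7 points |
| 5% / 2% | 0.60 × 0.95 = 0.570 | 0.47 × 0.98 = 0.461 | 10.9 points |
| 5% / 1% | 0.60 × 0.95 = 0.570 | 0.47 × 0.99 = 0.465 | 10.5 points |
| 2% / 2% | 0.60 × 0.98 = 0.588 | 0.47 × 0.98 = 0.461 | 12.7 points |
| 1% / 3% | 0.60 × 0.99 = 0.594 | 0.47 × 0.97 = 0.456 | 13.8 points |

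With equal rates both arms shrink by the same factor, and the 0.3-point change is only a matter of scale. With unequal rates the sign follows the imbalance: the stated definition overstates the experimental benefit in the first three rows and understates it in the last.

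**Effect on the test.** Log-rank simulation with 189 per arm, three years of follow-up for every patient, exponential DFS, non-tumour deaths in the first six months, and 6,000 runs per setting. All-cause DFS at 3 years was set equal in the two arms. The table gives the chance of a significant result in favour of the experimental arm at two-sided 0.05 (nominal 2.5%). Only an excess in that arm was simulated.

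| q experimental / control | Stated definition | Death from any cause |
|---|---|---|
| 0% / 0% | 2.6% | 2.6% |
| 2% / 0% | 4.2% | 2.5% |
| 3% / 1% | 3.6% | 1.9% |
| 5% / 1% | 6.3% | 2.0% |

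**Censoring date.** Kaplan-Meier 3-year DFS, censoring lost patients when last known alive minus censoring at the last scan, with six-monthly scans:
- 10% lost per arm, scans kept up: 0.6010 − 0.5981 = 0.3 points (experimental); 0.4737 − 0.4703 = 0.3 points (control).
- 10% lost per arm, last scan a further year back: 0.6110 − 0.5982 = 1.3 points; 0.4858 − 0.4702 = 1.6 points.
- 20% lost in the experimental arm and 5% in control: rises of 0.6 and 0.2 points with scans kept up, and 2.7 and 0.8 points with the extra year. The arm with more loss gains about 0.4 to 1.9 points on the difference.

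**The case against.** The strongest reply is that the size and direction rest on invented rates. That stands. A reader might infer that the definition favours radiotherapy, because the experimental arm adds 45 Gy with S-1. The article does not support this: the same arm receives six SOX cycles against eight in control, and no death rates by arm are given. The last row of the first table shows the bias running the other way.

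A reader might also infer that toxic deaths would be hidden. They would not. Overall survival counts every death, deaths are serious adverse events with expedited reporting, and the incidence of side effects is compared between arms. None of this changes what the primary test counts, however, and superiority is to be claimed on that test.

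Nor does the article say who assigns cause of death, so it cannot be said that unblinded staff do. What stands is that the definition requires the judgement and the trial is open label.

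On censoring, the rule is stated only for lost patients, and the visit schedule should keep most last contacts close to a scan. That is fair and makes this the minor part. One might multiply 10% of 378 (about 38 dropouts) by one unscanned year at 0.21 events per year and conclude that about 8 of 206 events go uncounted. That assumes a full unscanned year for every dropout. Censoring at the last scan would not recover those events either; it only removes the unchecked time.

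**Conclusion.** The point holds conditionally. As written, the primary endpoint leaves out deaths without recurrence that are judged unrelated to the tumour, and nothing else in the article corrects this. If such deaths differ between arms, the comparison is biased toward the arm with more of them. Which arm that would be, and by how much, cannot be read from the document. Over the assumed rates, 13 points on the stated definition corresponds to between 10.5 and 13.8 points of all-cause DFS. With an excess in the experimental arm, the one-tail false-positive rate is about 3.6% to 6.3% instead of 2.5%. These figures assume that non-tumour death is independent of recurrence; the simulation also places these deaths in the first six months.

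The censoring date is a real but secondary weakness. It shifts both arms by about 0.3 points if six-monthly CT is kept up, and by about 1.3 to 1.6 points if the last scan was a further year back, with 10% lost per arm. It favours one arm only if loss or scanning differs. The exit criterion for severe reactions makes such a difference possible but does not show it.

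**What to change.** Define DFS as the time from randomization to the first of locoregional recurrence, distant metastasis and death from any cause. Keep tumour-related death as a supportive cause-specific analysis. Censor patients without an event at their last disease assessment showing no recurrence (CT, endoscopy or biopsy).

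The cost is an amendment to the endpoint wording, made before analysis. Dates of death are already documented. The article does not say that the dates of negative scans are recorded, so the case report form should be checked for this. A few more events will count and DFS rates will be slightly lower. If the experimental arm does have more non-tumour deaths, a win becomes harder. In the same simulation with tumour-only DFS at 60% and 47%, the chance of a significant result at 3% versus 1% is about 72% on the stated definition and 60% with all deaths counted, because the true difference is smaller. The team should also confirm that the planned 47% and 60% apply to the revised endpoint.
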